**3. STUDY DESIGN**

**Design:** target trial emulation.

**Data source:** electronic health records from the clinical management system (CMS) of the Hong Kong Hospital Authority. Reference data for the available information is provided on a monthly basis.

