**4. STUDY POPULATION**

**Inclusion criteria:** The analysis will include all T2D patients aged ≥60 years with elevated low-density lipoprotein cholesterol (LDL-C) ≥2.6 mmol/L in each calendar month from January 2009 to December 2015. An LDL-C cut-off of 2.6 mmol/L is chosen as this represents the optimal treatment target for T2D patients with no prior history of CVD according to local guidelines (1).

**Exclusion criteria:** Patients who used statins before baseline, or used fibrates or any other lipid-lowering drugs classified under the British National Formulary code 2.12 before baseline will be excluded from the analysis. Individuals with a history of type 1 diabetes, CVDs, cancer, myopathies or liver dysfunction will be excluded. Patients with incomplete data for the study variables at baseline will also be excluded. Eligible patients need to have at least one follow-up visit record after baseline.

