**5. STUDY OUTCOME AND FOLLOW-UP PERIOD**

**Primary outcome:** major CVDs (i.e., a composite outcome of myocardial infarction, heart failure, stroke).

**Secondary outcome:** the three CVD subtypes, all-cause mortality, and muscle-related adverse events (AEs) and liver dysfunction.

After peer review, we also analyzed the composite outcome of major CVD diseases without heart failure as a sensitivity analysis for comparison, and expanded the assessment of muscle-related AEs to include myalgia, myositis, myopathy, and rhabdomyolysis.

Case definition was based on the International Classification of Primary Care, 2nd Edition (ICPC-2) and International Classification of Diseases, 9th Revision, Clinical Modification (ICD-9-CM), or relevant clinical parameters (Appendix I: S3 Table). We excluded patients with pre-existing diagnosed outcomes of interest on or before baseline to ensure the outcome events were restricted to the new incident cases occurring after baseline. The patients with documented old MI diagnosis (ICD-9 code: 412) or late effects of cerebrovascular disease (ICD-9 code: 438.x) on or before baseline were also excluded. For consistency, these two codes were also included in the case definitions for outcome events for MI and stroke. After peer review, we also conducted a sensitivity analysis where these two codes were excluded from the case definition of outcome events for comparison

Patients will be followed up until the outcome of interest, death, or the administrative end of our study (31 December 2018), whichever occurs first. Potential bias of undiagnosed disease might exist for the participants who experienced the outcome incidence within the first year of follow-up. After peer review, we retained these patients in the main analysis and conducted a sensitivity analysis by excluding these patients to test the potential bias (2).

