
**Subgroup analysis:** Subgroup analyses for the risk of overall CVD incidence and all-cause mortality will be conducted based on sex and Charlson Comorbidity Index (<8/≥8) at baseline.

**Sensitivity analysis**: Several sensitivity analyses were conducted. (1) To examine if the length of grace period for the ascertainment of statin discontinuation would have an impact on the results, a sensitivity analysis was conducted by extending this gap from 1 month to 3 months in per-protocol analysis. (2) To evaluate the residual confounding by indication, the patients with familial hypercholesterolemia at baseline were excluded in another sensitivity analysis. (3) An additional sensitivity analysis was conducted regarding the weight truncation at the cut-off of 20. After peer review, we additionally performed the sensitivity analyses below to test the robustness of our results: (4) To test whether the choice of LDL-C cut-off might influence the results, we performed a sensitivity analysis on all patients with T2DM. (5) Regarding the competing event of death, we conducted a sensitivity analysis of estimating the total effects, where death was not considered as a censoring event. (6) As mentioned, a sensitivity analysis was conducted by excluding the participants who had the outcome within the first year of follow-up. (7) As the main analysis was conducted in the matched sample, the estimation better reflects Average Treatment Effect on the Treated (ATT) rather than Average Treatment Effect (ATE). To investigate whether the estimated ATT would differ from the ATE in our study, we additionally performed a sensitivity analysis by including all eligible study participants before matching. (8) Finally, a sensitivity analysis was conducted by removing the exclusion criterion of requiring at least one follow-up visit after baseline. Instead, the person-trials were censored two years after their last recorded visit within the local public healthcare system (i.e., considered them lost to follow-up at this time point) and additionally applied inverse probability weights to account for censoring due to loss to follow-up. (9) For the primary composite outcome, we also analyzed the composite outcome without heart failure for comparison. (10) Finally, for the outcomes of MI and stroke, we performed a sensitivity analysis by excluding the old MI diagnosis (ICD-9 code: 412) or late effects of cerebrovascular disease (ICD-9 code: 438.x) in the case definition for outcome events after baseline.

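### Sensitivity analysis (8) sets the loss-to-follow-up date from the last recorded visit, so whether a patient is censored depends on what happens later, including the outcome

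*Protocol*

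**What the plan says.** Section 4 restricts the main analysis by attendance after baseline: "Eligible patients need to have at least one follow-up visit record after baseline". Section 5 then ends follow-up without any censoring for loss to follow-up: "Patients will be followed up until the outcome of interest, death, or the administrative end of our study (31 December 2018), whichever occurs first".

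Sensitivity analysis (8) in section 8, added after peer review, relaxes the restriction by "removing the exclusion criterion of requiring at least one follow-up visit after baseline". The rule that takes its place is that "the person-trials were censored two years after their last recorded visit within the local public healthcare system". A parenthesis gives the meaning attached to that date: "i.e., considered them lost to follow-up at this time point". As the adjustment for this censoring, the analysts "additionally applied inverse probability weights to account for censoring due to loss to follow-up".

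Nothing in section 8 says that the gap is judged month by month as follow-up proceeds. Nothing excludes the encounter that records the outcome from the visits that set the date.

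**The concern.** A censoring time should be decided by what is known up to that time. The last visit on record is not known until the record closes. Section 3 names one data source, "electronic health records from the clinical management system (CMS) of the Hong Kong Hospital Authority", and section 5 defines outcomes by diagnosis codes or clinical parameters. A non-fatal myocardial infarction, stroke or heart failure in that system is therefore itself a recorded contact, and it can move the date of the last visit forward. Events among long-absent patients are kept together with the gap before them, while the event-free time of comparable patients is cut at 24 months.

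At stake is the only listed analysis that censors for loss to follow-up and drops the visit requirement. If its censoring is tied to the outcome, neither agreement nor disagreement with the main result can be read at face value.

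**Working it through.** The plan states no figure on this point, so there is none to reproduce.

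**1. Can such gaps arise?** Baselines run "in each calendar month from January 2009 to December 2015" and follow-up ends on 31 December 2018, so potential follow-up is about 3 to 10 years. A gap of more than two years is possible in every emulated trial.

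**2. Two patients, both last seen at month 0.**

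| | Rule as worded | First 24-month gap |
|---|---|---|
| P1: admitted with MI at month 40 | last visit becomes month 40, censoring date month 64; 40 months and 1 event counted | censored at month 24, no event |
| P2: never returns | censored at month 24, no event | censored at month 24, no event |

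Up to month 24 the two histories are identical. Only the future separates them. Weights conditional on history give P1 and P2 the same censoring probability, so they cannot undo the selection. This is an argument from the structure of the weights; no weighted analysis was simulated.

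**3. Effect within leavers (assumed values).** Let λ be the event rate and R the years left after the last routine visit, with all events recorded and no other returns. For R > 2, under the rule as worded:

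- expected events = 1 − exp(−λR)
- expected person-years = [1 − exp(−λR)(1 + λR)]/λ + 2·exp(−λR)

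With λ = 0.036 per year and R = 5.5:

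- events = 1 − exp(−0.198) = 0.1796
- person-years = [1 − 0.8204 × 1.198]/0.036 + 2 × 0.8204 = 0.478 + 1.641 = 2.118 (unrounded inputs)
- rate = 0.1796/2.118 = 0.0848 per year, or 2.36 times the true 0.036

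With the first-gap rule: events = 1 − exp(−0.072) = 0.0695, person-years = 0.0695/0.036 = 1.930, rate = 0.036. No bias.

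**4. Effect on a whole arm.** Add the time before leaving to the leavers' time and average over exponential leaving times. Follow-up is 7.5 years (90 months), λ is 2.4%, 3.6% or 6.0% per year, the true ratio is 1, and all events are recorded.

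| Leaving per year, initiators / non-initiators | Arm rate ÷ truth, as worded | Rate ratio, as worded | Rate ratio, first gap |
|---|---|---|---|
| 2.4% / 2.4% | 1.04 / 1.04 | 1.00 | 1.00 |
| 2.4% / 4.8% | 1.04 / 1.08–1.09 | 0.96–0.97 | 1.00 |
| 2.4% / 7.2% | 1.04 / 1.11–1.13 | 0.92–0.93 | 1.00 |

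A separate monthly simulation used 400,000 patients per arm, 6.5 years, leaving at 2–5% versus 5–20% per year, and returns for other reasons at 0 or 20% per year. When leaving differed by arm it gave 0.834–0.986 as worded and 0.996–1.014 with the first gap. Returns for other reasons shrink the bias.

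**5. Incomplete recording of leavers' events.** Same 90-month setting, no returns for other reasons, true ratio 1. The last column is the main analysis, with no loss-to-follow-up censoring.

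| Recorded | Leaving per year | As worded | First gap | Main |
|---|---|---|---|---|
| All | 2.4% / 4.8% | 0.96–0.97 | 1.00 | 1.00 |
| Half | 2.4% / 4.8% | about 1.00 | 1.02 | 1.04–1.05 |
| Half | 2.4% / 7.2% | 0.99–1.00 | 1.04 | 1.08–1.09 |
| None | both | 1.04–1.09 | identical | 1.09–1.20 |

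At half capture the rule as worded lands near 1 because two errors cancel. The first-gap rule still carries the missed-event error, which is a separate problem.

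**6. Deaths.** A death that reaches the record without a visit, more than two years after the last visit, falls after the censoring date and is dropped. That error runs in the opposite direction.

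**The case against.** **The wording can bear another reading.** The models are pooled logistic with weights at each time point, and in that setting the last visit could mean the most recent one as of each month. On that reading the defect disappears. This is possible, but the text does not say it, and a censoring rule that the protocol does state should not depend on a charitable reading.

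**An outcome admission may not count as a visit.** Neither section 4 nor section 8 defines a visit. If outcome encounters were excluded, the direct link to the outcome would go, but any later return for another reason would still remove the censoring in retrospect.

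**The size and direction are assumed.** This stands. The ratio is biased only if attendance differs by arm, and the matching factors include prior-year specialist clinic attendance and hospitalization. If initiators left more often, the direction would reverse. A reader might infer that the rule makes statins look protective; the protocol has no attendance data by arm to support that.

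**False reassurance is not shown.** A reader might infer that agreement between this check and the main result hides a bias. With full recording, where the rule's own bias is not masked by missed events, the main analysis is at 1.00, so the error is a false alarm. Where events are missed, the rule as worded can sit closer to 1 than either the main analysis or the first-gap rule, though only by cancellation.

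**Returning patients are not exempt from censoring altogether.** They are not censored before the event or return that brings them back; they can be censored later.

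**Conclusion.** The point holds on the plain wording. Sensitivity analysis (8) lets later information, including the outcome, decide whether a person-trial is censored, and the stated weights cannot remove this.

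When leavers' events are recorded, arm-specific rates and absolute risks are inflated. If attendance also differs by arm, the hazard ratio is biased: 0.92–0.97 for a true 1 under two- to three-fold differences in leaving, no returns for other reasons and complete recording, and 0.834–0.986 over the wider range. These are crude, unmatched and unweighted rate ratios under assumed rates. The document supplies neither attendance nor event capture, so the actual size and direction are unknown.

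The consequence is limited: this check can disagree with a sound main analysis, or look unbiased only through offsetting errors. It would be tempting to read this as a flaw in the main result. The documents do not support that, because the main analysis does not use this rule.

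**What to change.** Censor each person-trial at the first time 24 months pass without a recorded visit, whether or not the patient returns. Count no events after that time, fit the loss-to-follow-up weights to this time-updated indicator, and rerun sensitivity analysis (8). State which encounters count as a visit and how a death recorded without a visit is handled. If the analysts already used the most recent visit at each month, one sentence saying so is enough.

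The cost is a change to the code that builds the censoring date, a rerun of one sensitivity analysis, and the loss of some late events in returning patients, with slightly lower precision. The change does not address events that never reach the public record; that limitation should be stated alongside the result.

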**9. RELEVANT RESEARCH CHECKLIST**

This study is reported as per TrAnsparent ReportinG of studies Emulating a Target trial (TARGET) guideline.

